## Abstract

**Background:**

Maintaining mobility in old age is crucial for healthy ageing including delaying the onset and progress of frailty. However, the extent of an individuals´ mobility relies largely on their personal, social, and environmental resources as outlined in the Life-Space Constriction Model. Recent studies mainly focus on facilitating habitual out-of-home mobility by fostering one type of resources only. The MOBILE trial aims at testing whether tablet-assisted motivational counselling enhances the mobility of community-dwelling older adults by addressing personal, social, and environmental resources.

**Methods:**

In the MOBILE randomized controlled trial, we plan to enrol 254 community-dwelling older adults aged 75 and older from Havelland, a rural area in Germany. The intervention group will receive a tablet-assisted motivational counselling at the participant´s home and two follow-up telephone sessions. Main focus of the counselling sessions lays on setting and adapting individual mobility goals and applying action planning and habit formation strategies by incorporating the personal social network and regional opportunities for engaging in mobility related activities. The control group will receive postal general health information. The primary mobility outcome is time out-of-home assessed by GPS (GPS.Rec2.0-App) at three points in time (baseline, after one month, and after three months for seven consecutive days each). Secondary outcomes are the size of the GPS-derived life-space convex hull, self-reported life-space mobility (LSA-D), physical activity (IPAQ), depressive symptoms (GDS), frailty phenotype, and health status (SF-12).

**Discussion:**

The MOBILE trial will test the effect of a motivational counselling intervention on out-of-home mobility in community-dwelling older adults. Novel aspects of the MOBILE trial include the preventive multi-level intervention approach in combination with easy-to-use technology. The ecological approach ensures low-threshold implementation, which increases the benefit for the people in the region.

**Trial registration:**

The MOBILE trial is prospectively registered at DRKS (Deutsches Register Klinischer Studien, German Registry of Clinical Trials) DRKS00025230. Registered 5 May 2021.

## Background

Due to current and future changes in demographic society distributions, more attention must be paid to the aspect of healthy ageing [1]. Healthy ageing is challenged as people get older is the growing prevalence of the frailty syndrome that varies from 4 to 59% depending on the used conceptualisation, assessments, and defined age group [2]. Frailty is characterised by reduced physical reserves, activity restrictions, and a low-level of social participation leading to a decreased ability to cope with everyday stressors, a higher risk of adverse health outcomes, and overall reduced mobility [3, 4]. Therefore, interventions to prevent or delay the onset of frailty that are easy to apply and scalable are crucially needed. One way of preventing or delaying frailty is the facilitation of out-of-home mobility [5], as it is a prerequisite for participation in physical activities, social in-person involvement, and access to health care [6, 7]. Out-of-home mobility can be can be defined as movement through outdoor living environments called life-spaces expanding from one´s home to the neighbourhood, city lived in, and beyond [7, 8].

According to the Life-Space Constriction model, a person´s out-of-home mobility is determined by a combination of personal (e.g., health status, health literacy, coping strategies), social (e.g., social network, connection to neighbourhood), and environmental (e.g., regional infrastructure, access to health care) resources and obstacles [9], indicating that multi-level interventions on facilitating out-of-home-mobility seem to be most promising [5, 9]. Although the Life-Space Constriction model proposes the combination of individual, social and environmental resources and although there is evidence from longitudinal studies on the relationship between social factors and mobility [10] most interventional studies largely relied on addressing personal resources only. Personal goal setting and motivational support seem to be promising components as highlighted in the AGNES trial [11]. This applies especially when used techniques are based on well-founded psychological theories such as coping with loss or onset of disability as well as self-regulatory strategies to change behaviour [12, 13]. There is little evidence about the use of behaviour change techniques to maintain or modify out-of-home mobility in interventions to prevent frailty and one promising but solemnly used technique may be the formation of routines/habits [14, 15]. In addition results of a recent intervention study in Finland suggest that more evidence is needed on the short- and long-term effects of face-to-face counselling interventions addressing participation in mobility-related activities [16]. However, in the Finnish study, out-of-home mobility was solely measured using self-reported instruments. There is a growing body of evidence that out-of-home mobility is measured more precisely using Global Positioning Systems (GPS) data rather than the commonly used self-reported questionnaires [17]. Additionally there is existing evidence that out-of-home mobility is notably restricted in those older adults living in rural areas due to less infrastructure, car-dependency, and difficult access to health care, indicating the need of intervention studies in rural areas [18]. Hence, little research has been done when it comes to combining individual goal setting with social and environmental resources in a multi-component intervention with objective GPS measurements, especially when focusing on prevention or reversing frailty in older adults in rural areas [5, 19, 20]. To close the defined research gaps, the MOBILE (Mobility in Old age By Integrating health care and personal network resources in older adults Living in rural arEas) trial is aiming to determine whether a motivational counselling intervention can facilitate out-of-home mobility in older adults living in rural areas.

### Objectives

The main objective of the MOBILE trial is to test the effectiveness of a motivational counselling intervention to improve out-of-home mobility and thereby possibly preventing or delaying frailty in community-dwelling older adults in a particular rural area. Furthermore, drawing on the Life-Space Constriction model, we will be investigating the resources at personal, social, and environmental level and their relationship with out-of-home mobility, which, in turn, will be related with indicators of health, wellbeing, and frailty.

## Methods/design

### Trial design

The MOBILE trial is a randomized controlled interventional study using a pragmatic sample comparing an intervention to facilitate out-of-home mobility with generic health and mobility information that apply to the participants living area. Data will be collected as Computer Assisted Personal Interview (CAPI) and Computer Assisted Telephone Interviews (CATI) on five points in time (T_0_ – T_4_) and will consist of questionnaires, assessments, and objective GPS measurements. At baseline (T_0_) a comprehensive questionnaire consisting of established valid scales focusing on personal, social, and environmental resources is conducted as CAPI by a trained study nurse. Furthermore, physical assessments (i.e., mobility and walking test, handgrip) will be included at baseline. T_1_ is planned as a short questionnaire after the first intervention session including change-sensitive scales to capture immediate intervention effects, whereas T_2_ will serve as a follow-up measurement where most parts of the baseline questionnaire (excluding sociodemographic variable) are repeated. T_3_ and T_4_ are short telephone-based interviews with focus on personal resources. An overview of the used scales and assessments at each measuring point is outlined in Table 1.

**Table 1 Tab1:** Outcome Measure of the MOBILE trial

Outcome Measure		Operationalisation (Type of assessment)	Times of assessment					Ref
**Main Outcome**			T_0_	T_1_	T_2_	T_3_	T_4_	
Time out-of-home	GPS tracker for seven consecutive days		S	S	S	-	-	[25]
**Secondary Outcomes**								
Life-Space parameter	Aggregated GPS data (i.e. convex hull)		S	S	S	-	-	[25]
Self-perceived life-space	LSA-D		H	H	H	T	T	[6]
Physical activity	IPAQ		H	H	H	-	-	[29]
Depressive symptoms	GDS-12R		H	-	H	-	-	[30]
Health Status	SF-12		H	H	H	-	T	[32]
Frailty	Frailty-phenotype Fried		H	-	H	-	T	[34]
**Mediator variables**								
Goal attainment	Selected items from SOC-questionnaires		H	H	H	-	-	[46]
Habits	4 items from SRHI		H	H	H	-	-	[47]
Lifestyle chance	Action and coping planning, adapted from Schwarzer et al. 2008		H	H	H	-	-	[48]
Balance confidence	ABC-6		H	-	H	-	-	[49]
Health literacy	HLS-EU-Q16		H	-	H	T	T	[50]
Views on ageing	Adapted from DEAS survey		H	-	H	-	-	[51]
Connection to place	Selected items from housing enabler questionnaires		H	-	-	-	-	[52]
Access to health care	Own items		H	-	-	-	-	-
Utilization of health care	Own items		H	-	-	-	-	-
Connection to neighbourhood	Selected items from DEAS survey		H	-	-	-	-	[53]
Social network	Adapted from SHARE survey		H	-	H	-	-	
Loneliness	UCLA Three-Item Loneliness Scale		H	-	H	-	-	[54]
Social Participation	Own items, adapted from SHARE survey		H	-	H	T	T	[51]
**Covariates**								
Sociodemographic data	Age, gender education level, level of care, living arrangements		H	-	-	-	-	-
Physical performance	DEMMI		H	-	H	-	-	[55]
Hand grip	Gauged Hand grip dynamometer, Sahean SH5001		H	-	H	-	-	-
History of falls	Single-item question		H	H	H	T	T	-
Utilization of assistive devices	Own questions, adapted from Baker, 2003		H	-	-	-	-	[6]
Cognition	Mini-Cog		H	-	-	-	-	[56]
Corona	Covid-19 history, vaccination status, anxiety, impact on daily life (own items, single-questions)		H	-	-	-	-	-
Living surroundings, observation by interviewer	Type of house, stairs in front or within the building, pavement		H	-	-	-	-	-

*H,* Home based interview CAPI, *S* self-assessment of GPS-Data with study mobile phone, *T* Telephone-based interview *CATI*, *T*_0_ Baseline measurement, *T*_*1*_ one months after baseline, *T*_*2*_ three months after baseline, *T*_*3*_ 6 months after baseline, *T*_*4*_ 12 months after baseline, *Ref*. reference, *GPS* Global Positioning System, *LSA-D* German version of the University of Alabama Life-Space Assessment, *IPAQ* International Physical Activity Questionnaire, *GDS-12R* short residential Version of the Geriatric Depression Scale, *SF-12* The Short Form Health Survey, *SOC* Selection, Optimization, and Compensation, *SRHI* Self-Report Index of Habit Strength, *ABC-6* Activity-specific Balance Confidence scale *HLS-EU-Q16* Health Literacy Scale, 16 items, *DEAS* German Ageing Study / Deutscher Alterssurvey, *SHARE* The Survey of Health, Ageing and Retirement in Europe, *DEMMI* De Morton Mobility Index, *Mini-Cog* Screening for Cognitive Impairment in Older Adults

All participants will be equipped with needed technology to track the GPS coordinates and activity diaries measuring out-of-home mobility at three points in time (as outlined in Fig. 1 ) for seven consecutive days each. GPS data is measured using a study mobile phone (ZTE Blade A5) with the “GPS.Rec2.0”-App as the only working application. The app was developed solely for the purpose of this trial and was tested and adapted as part of piloting work. “GPS.Rec2.0” is a mere data collection app and there is no interaction with the study participant. GPS location is recorded every ten seconds with an accuracy of up to 25 m. A detailed description and availability on the technical development of the “GPS.Rec2.0” application is going to be published elsewhere.

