#### Adaptions due to Corona-pandemic

As the Covid-19 pandemic is both unpredictable and dynamic, changes in the execution of the intervention and questionnaires at T_0_, T_1_, and T_2_ may become necessary. If the situation requires it, we will switch to remote option for the aforementioned tasks. To minimize the risk of infections in general, all contacts with participants will take place in compliance with hygiene regulations of Charité – Universitätsmedizin Berlin and federal state of Brandenburg. Key components of the MOBILE hygiene concept include full vaccination of study personal, wearing FFP2-masks, sanitizing, and ventilation at scheduled intervals. Although protocol deviations may occur due to the pandemic, the main components of the trial, i.e., assessment of study variables and delivery of the intervention will still be feasible, albeit with adjustments, such as telephone instead of personal interviews.

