#### Outcomes

## Primary outcome

The primary outcome variable is “time out-of-home” (TOH) based on the objective GPS measurement and meaning the total time spent outside of one´s home radius (i.e. 50 m) per day. TOH can be measured in minutes or percentage. A day in this connection is defined from 3:00 AM to 02:59 AM to include trips than last longer than midnight and as recommended in literature [25, 26]. GPS data is monitored on seven consecutive days at T_0_, T_1_, and T_2_ respectively. An overview of all outcomes, assessments and time of measurement is demonstrated in Table 1.

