### Recruitment of participants

A number of complementary strategies will be employed for the recruitment of participants. First approaches include a newspaper article, displaying of study information flyer on designated spots (e.g., supermarkets, pharmacies, health or public institution), and recruitment via our stakeholder network. Further steps will include postal invitations to all citizen of Havelland aged 75 and older (data has been provided by the public register for the purpose of this trial), presentation of our trial on various occasions (e.g., sport groups, social activities, public events), internet magazine articles, and advertisement. We implemented a website, a flyer, and posters to complement our recruitment strategy. Recruitment success of each path and strategy will be tracked and readjusted if applicable. Once an interested person contacts the MOBILE study team, the initial screening for eligibility (age, place of living, mobility) will be performed via phone, where questions can be asked and the further course of the study will be explained. Those, who are interested and eligible, will then receive the study information letter, consent forms, and hygienic concept via post. Informed consent form will be collected at the baseline measurement (T_0_) once the initial screening is confirmed by the study nurse. Study participants receive no financial compensation, however all participants get to keep the bumbag with the study emblem printed on, that was given to them with the GPS-tracker.

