#### Trial status

Rolling recruitment started on 7 June 2021 (i.e., first participant in) for a duration of presumably 12 months, meaning that the last participants included in the study will have their baseline assessment in June 2022 und their last assessment one year later in June 2023 marking the end of the field phase. Recruitment can be extended by up to six months, if the required number of participants has not yet been reached. The funding period for this trial is until February 2024.

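### No season or calendar term is named for time out-of-home under year-round recruitment, and pandemic impact is recorded only at baseline: a modest loss of precision and a possible confounder of the resource-mobility analysis

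*Protocol article*

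**What the plan says.** The primary outcome is the "total time spent outside of one´s home radius (i.e. 50 m) per day" (Primary outcome). The schedule is fixed: "GPS data is monitored on seven consecutive days at T_0_, T_1_, and T_2_ respectively". The footnote to Table 1 places T1 one month and T2 "three months after baseline".

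On calendar time, Trial status says: "Rolling recruitment started on 7 June 2021 (i.e., first participant in) for a duration of presumably 12 months". It adds that "Recruitment can be extended by up to six months". The section on adaptations to the pandemic begins: "As the Covid-19 pandemic is both unpredictable and dynamic". The adaptations it then lists concern remote delivery and hygiene, not the analysis.

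The covariate block of Table 1 has eight rows: sociodemographic data, physical performance, hand grip, falls, assistive devices, cognition, Corona, and living surroundings. The Corona row reads "Covid-19 history, vaccination status, anxiety, impact on daily life (own items, single-questions". It is marked as a home interview at T0 and with a dash at T1 to T4. The Statistical analysis section names a multilevel model across T0-T2 for the primary hypothesis and a covariance analysis for resources and mobility, with no season or calendar term in either. Under Objectives, the relation between resources and out-of-home mobility is an aim in its own right.

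**The concern.** A person enrolled in July has T2 in October; one enrolled in February has T2 in May. If time away from home follows the seasons, the expected change from T0 to T2 differs in size and sign by month of entry, whatever the intervention does. Public restrictions may add a second calendar pattern.

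Two things are at stake. In the randomised comparison, calendar variation that is not modelled goes into the residual and widens the confidence interval. In the resource-mobility analysis nothing is randomised. A resource that itself moves with season or restrictions, such as social participation or loneliness (both in Table 1 at T0 and T2), can then appear related to mobility because both follow the calendar.

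The pandemic item differs from the season term in one respect. Season can be rebuilt from dates at any time. A question not asked at T1 and T2 cannot be recovered by any later analysis plan.

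**Working it through.** **1. The plan's own figure.** Inputs from Sample size: Life Space 65.4 against 75.2 (difference 9.8), SD 20.1, two-sided alpha 5%, power 95%, ratio 1:1.

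n per arm = 2 × (1.960 + 1.645)² × (20.1 / 9.8)² = 2 × 12.99 × 4.207 = 109.3, so 110. With 15% added: 110 × 1.15 = 126.5, so 127 per arm and 254 in total. The stated figure reproduces. It is a plain comparison of two means on a Life Space score, with no credit for baseline and no allowance for season.

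**2. Bias in the treatment comparison.** Simulation with 220 analysed, blocks of 4, even entry over 12 months, a cosine season effect, non-seasonal T0-T2 correlation 0.5, no treatment effect, and T2 adjusted for T0:

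| Season amplitude (SD) | Mean estimate, season omitted | SE, season omitted | SE, season modelled | Type I error, omitted / modelled |
|---|---|---|---|---|
| 0.25 | -0.001 | 0.120 | 0.117 | 4.2% / 4.7% |
| 0.5 | -0.002 | 0.128 | 0.117 | 3.2% / 5.1% |

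There is no bias. The model-based SE is about 2.5% and 10% too large and the test is conservative. The protocol's blocks of 4, 6 and 8 within strata would balance calendar time somewhat less tightly, but allocation is still random and concurrent.

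**3. Size of the variance cost.** Assumptions: non-seasonal variance 1, correlation between waves r = 0.6, a yearly sine wave of amplitude A, even entry over the year. The variance at each wave is V = 1 + A²/2.

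- Covariance of T0 with T2 (a quarter-year, cos 90° = 0): 0.6.
- Covariance of T0 with T1 (one month, cos 30° = 0.866): 0.6 + 0.866 × A²/2.
- Residual variance given T0: V − cov²/V. With season modelled it is 1 − 0.36 = 0.64.

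| A | V | T2 residual | Ratio to 0.64 | Sample loss, 1 − 1/ratio | T1 residual | Ratio to 0.64 |
|---|---|---|---|---|---|---|
| 0.2 | 1.020 | 0.667 | 1.04 | 4% | 0.646 | 1.01 |
| 0.3 | 1.045 | 0.701 | 1.09 | 9% | 0.654 | 1.02 |
| 0.4 | 1.080 | 0.747 | 1.17 | 14% | 0.665 | 1.04 |

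For a simple T0-T2 change score the ratio is (0.8 + A²)/0.8 = 1.05, 1.11 and 1.20.

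**4. Cross-check on the plan's own scale.** Suppose the SD of 20.1 excludes season, and season makes up a share R² of the total variance, so that the SD becomes 20.1/√(1 − R²). Power at 110 per arm, starting from 95.1%:

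| R² | SE factor | Power | n per arm for 95% |
|---|---|---|---|
| 2% | 1.01 | 94.7% | 112 |
| 5% | 1.03 | 94.1% | 116 |
| 10% | 1.05 | 92.9% | 122 |
| 15% | 1.08 | 91.5% | 129 |
| 20% | 1.12 | 89.9% | 137 |

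If 20.1 already contains seasonal variation, modelling it would instead raise power to between 95.5% and 98.1%.

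**5. Confounding of the resource analysis.** The article gives no figures from which this could be computed. The pathway needs calendar time to move both the resource and mobility. That is plausible for social participation, loneliness and habits. It is weak for resources measured once and slow to change, such as connection to place.

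**The case against.** The strongest reply is that Table 1 is a schedule of instruments, not an adjustment set. Season is not an instrument, it follows from dates already held, and a condensed article may leave model covariates to an analysis plan that is not shown. This stands in part: the missing season term is not an error in the document, and it can still be added. It does not cover the pandemic item, whose T0-only schedule is fixed here although Trial design says that T2 repeats most of the baseline questionnaire and the falls question is asked at all five time points.

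A second reply is that the precision cost is small, assumed and largest at T2. That stands. Even at A = 0.4 the baseline-adjusted residual variance, 0.75, is below the value of 1 that corresponds to a sample size without baseline adjustment. On these assumptions, season alone does not undo the planned precision.

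Third, a repeated pandemic item would be measured after allocation and so is unsuitable as a covariate in the treatment comparison. That also stands, and it limits the item to description.

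Two stronger readings are tempting:

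- A reader might infer that season biases the treatment effect. Concurrent blocked randomisation rules that out.
- A reader might infer that the resource-mobility association is confounded because recruitment is staggered: "Further steps will include postal invitations to all citizen of Havelland aged 75 and older". The article gives an order of steps but no dates, calls the strategies complementary, and does not say how participants differ by route. Only possible confounding is supported.

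**Conclusion.** The point holds as a minor, inexpensive improvement. The facts are plain: GPS weeks spread over three months, entry at any time of year, no season or calendar term named, and pandemic impact asked once.

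The primary comparison stays unbiased. The cost in precision is about 4-17% more residual variance at T2, equivalent to losing about 4-14% of the sample, and about 1-4% more at T1. These sizes rest on an assumed amplitude of 0.2-0.4 SD, a correlation of 0.6 and even entry over the year; the article supports none of these numerically. The 17% is a variance increase and should not be read as a sample loss.

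For the resource objective, season and pandemic phase can confound associations with time-varying resources, to an unknown degree. At T0 the Corona items allow some adjustment, so the pandemic gap concerns T1, T2 and change over time. The T0-only schedule is the firmer part, because it alone cannot be repaired afterwards.

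**What to change.** - **Mobility models (time out-of-home and convex hull):** prespecify a time-varying season term for each GPS week, from its dates. Sine and cosine of calendar date is the safer choice, because the outcome includes time spent indoors elsewhere; day length is an alternative.
- **Resource-mobility models:** include the same season term, plus calendar period or the dated level of public restrictions.
- **Pandemic item:** repeat the daily-life impact question at T1 and T2, for description only. Do not use it as a covariate in the treatment comparison, since allocation could affect the answer.
- **Recruitment route:** do not adjust for it in the main resource model. Some routes run through sport groups, social activities and the stakeholder network, so route may stand in for the social resources under study. Use it at most in a sensitivity analysis.

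The cost is a few degrees of freedom and one extra question in interviews that already take place. The calendar terms can be applied to participants already enrolled; the repeated item helps only for interviews still to come.
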